## Abstract

**Background:**

Informed consent is a legal and ethical prerequisite for psychotherapy. However, in clinical practice, consistent strategies to obtain informed consent are scarce. Inconsistencies exist regarding the overall validity of informed consent for psychotherapy as well as the disclosure of potential mechanisms and negative effects, the latter posing a moral dilemma between patient autonomy and nonmaleficence.

**Objective:**

This protocol describes a randomized controlled web-based trial aiming to investigate the efficacy of a one-session optimized informed consent consultation.

**Methods:**

The optimized informed consent consultation was developed to provide information on the setting, efficacy, mechanisms, and negative effects via expectation management and shared decision-making techniques. A total of 122 participants with an indication for psychotherapy will be recruited. Participants will take part in a baseline assessment, including a structured clinical interview for Diagnostic and Statistical Manual of Mental Disorders-fifth edition (DSM-5) disorders. Eligible participants will be randomly assigned either to a control group receiving an information brochure about psychotherapy as treatment as usual (n=61) or to an intervention group receiving treatment as usual and the optimized informed consent consultation (n=61). Potential treatment effects will be measured after the treatment via interview and patient self-report and at 2 weeks and 3 months follow-up via web-based questionnaires. Treatment expectation is the primary outcome. Secondary outcomes include the capacity to consent, decisional conflict, autonomous treatment motivation, adherence intention, and side-effect expectations.

**Results:**

This trial received a positive ethics vote by the local ethics committee of the Center for Psychosocial Medicine, University-Medical Center Hamburg-Eppendorf, Hamburg, Germany on April 1, 2021, and was prospectively registered on June 17, 2021. The first participant was enrolled in the study on August 5, 2021. We expect to complete data collection in December 2022. After data analysis within the first quarter of 2023, the results will be submitted for publication in peer-reviewed journals in summer 2023.

**Conclusions:**

If effective, the optimized informed consent consultation might not only constitute an innovative clinical tool to meet the ethical and legal obligations of informed consent but also strengthen the contributing factors of psychotherapy outcome, while minimizing nocebo effects and fostering shared decision-making.

**Trial Registration:**

PsychArchives; http://dx.doi.org/10.23668/psycharchives.4929

**International Registered Report Identifier (IRRID):**

DERR1-10.2196/39843

## Introduction

Obtaining patients’ informed consent represents a legal and ethical obligation for conducting psychotherapy, which is embedded in numerous codes of conduct of international psychological institutions (eg, American Psychological Association [1], European Federation of Psychologists’ Associations [2]). Psychotherapists are legally bound to disclose information about the treatment, including all circumstances that might be essential for an autonomous decision (eg, § 630e, German Civil Code [3]). In an ethical framework, psychotherapists should strive to balance the 4 moral principles of respect for autonomy, beneficence, nonmaleficence, and justice [4]. The major components of a truthful informed consent are (1) the decision-making capacity of the patient, (2) disclosure of treatment information, (3) voluntariness, (4) patient understanding, and (5) the explicit statement of consent [4,5].

A key challenge in obtaining truthful informed consent is the required disclosure of the potential negative effects of psychotherapy. Balancing the principles of autonomy and nonmaleficence causes an ethical dilemma [6]. On the one hand, psychotherapists strive to provide transparent information about possible treatment risks to enable autonomous informed decision-making. On the other hand, the disclosure of risk information can be harmful in itself, as it might cause nocebo effects. The latter effects are usually described as adverse effects that are not caused by the procedure but by negative expectations or negative prior learning experiences [6,7]. Thus, patients who were initially informed about the potential side effects at the beginning of psychotherapy are suggested to be more likely to experience these disclosed side effects than patients who did not receive this information before.

In clinical practice, informed consent procedures often fall short of legal and ethical recommendations of truthful informed consent [8,9]. So far, informed consent does not seem to be an integral part of clinical routine [10,11]. Empirical research, however, provides evidence that patients experiencing mental disorders have extensive information and decision-making needs [12,13]. Thus, a one-size-fits-all approach for providing consent information that neglects individual information needs may be insufficient.

Recent research suggests that the informed consent procedure might be underestimated in its clinical relevance to strengthen the contributing factors of psychotherapy outcome [5]. There are already first indications that the disclosure of transparent and contextualized information can effectively optimize treatment expectations [14]. Since treatment expectations are considered a key mechanism of change in psychotherapy [15], it is conceivable that truthful informed consent might elicit relevant expectation effects that reinforce treatment outcome [5,16]. Moreover, the autonomous treatment motivation and treatment adherence of patients might be strengthened [17,18]. However, it remains unclear how these key predictors of psychotherapy outcome can be optimally addressed in a tangible informed consent procedure.

Framing, contextualization, and shared decision-making might represent 3 promising strategies to optimize informed consent procedures. First, positive information framing might contribute to overcoming the dilemma of presenting transparent information about risks of psychotherapy on the one hand and preventing nocebo effects on the other hand [19]. Empirical findings suggest that positive framing may reduce side-effect expectations [14] and nocebo side effects [20]. Second, contextualizing information might positively influence treatment expectations and reduce decisional conflicts [6,14]. Third, integrating shared decision-making strategies might promote patient-centered care [21,22]. Advanced approaches for addressing, integrating, and implementing those strategies within an elaborate informed consent procedure are still missing in clinical practice to this day [20,23].

In summary, 3 major research gaps can be identified. First, empirical data about whether and how psychotherapists obtain informed consent in clinical practice are sparse. In particular, the integration of risk information has not been investigated so far. Second, there is a lack of concrete implementation strategies for an informed consent procedure that simultaneously accounts for legal, ethical, and clinical functionalities. Third, the effects of informed consent procedures on factors contributing to psychotherapy outcomes have not yet been investigated systematically. The latter 2 research gaps will be specifically targeted in this study. An optimized informed consent consultation (OIC) for psychotherapy has been developed as a new clinical tool based on the most recent empirical evidence. OIC will be applied in a web-based context for 2 reasons: (1) to increase accessibility and (2) to reduce health risks due to the ongoing pandemic. As the web-based context requires access to the internet for all participants and the study staff, potential interferences due to internet connection problems will be considered by providing clear instructions to participants with backup weblinks and contact information via phone.

This study aims to investigate the efficacy of OIC for persons with an indication for psychotherapy. We hypothesize that treatment expectations, autonomous treatment motivation, and adherence intention increase to a greater extent in the OIC condition than in the treatment as usual (TAU) condition from baseline (T0) to the follow-up assessment (T2). Moreover, we assume that decisional conflicts and expectations about the side effects of psychotherapy decrease to a greater extent in the OIC condition than in the TAU condition from baseline (T0) to the follow-up assessment (T2).

## Methods

### Study Design

A randomized controlled superiority trial will be conducted in the web-based context. Participants with an indication for psychotherapy are equally assigned to one of the 2 trial conditions (either to OIC + TAU or to TAU alone). The trial includes 2 web-based study visits with an interval of 2 weeks between the visits and 2 follow-up assessments 2 weeks and 3 months later. Web-based study visits are conducted via RED connect, an internet platform providing video consultations compliant with the German Data Protection Directive. Written study information, informed consent, and questionnaire-based assessments are provided via the web-based software EFS Survey, which fulfills the international guidelines for information security (ISO 27001). This study has been designed in line with the Consolidated Standards of Reporting Trials (CONSORT) statement [24].

### Participants

#### Recruitment

The target population for the trial are German adults with an indication for psychotherapy. Recruitment cooperation with the outpatient clinic of the Center for Psychosocial Medicine at the University Medical Center Hamburg-Eppendorf was instated. In addition, participants will be recruited through referrals from other cooperating outpatient facilities, physicians, psychotherapists, mailing lists, internet platforms, and social media.

#### Inclusion and Exclusion Criteria

Participants need to (1) be older than 18 years of age, (2) have an indication for psychotherapy, (3) have an email account and a web-connected device with a camera and a microphone, and (4) provide informed consent for study participation and the use of an audio record. The indication for psychotherapy will be operationalized by at least one suspected diagnosis according to the Diagnostic and Statistical Manual of Mental Disorders-fifth edition (DSM-5) [25].

Exclusion criteria are (1) a current outpatient or inpatient psychotherapy, (2) utilization of probatory sessions for psychotherapy within the last 4 weeks, (3) insufficient language comprehension, (4) insufficient attention performance or cognitive capacity to participate in the interviews and OIC, and (5) acute suicidality. Exclusion criteria (3) and (4) will be evaluated by the study psychologist during the telephone screening and the clinical interview. Based on a criteria-led graduated scheme, acute suicidality will be evaluated by the study psychologist within the clinical interview. In case of acute crises, further predefined steps for action will be initiated.

#### Sample Size

The required sample size was a priori calculated using the G*Power software. Based on a previous experimental study analyzing the effects of framing and personalizing information about endocrine treatment on side-effect expectations in healthy women [14], a small-to-medium effect size can be expected for the impact of OIC on the primary outcome (treatment expectations). For two-tailed testing and a predetermined α level of .05, 106 participants would provide 80% power to detect significant interaction and the main effects of Cohen *f*=0.125 on the primary outcome. To compensate for an anticipated dropout rate of 15%, a total sample of 122 participants will be randomly assigned to one of the 2 groups (n=61 per group). Since it is assumed that at least 50% of all individuals can be included in the clinical trial after screening, approximately 244 individuals will need to be screened (see Figure 1).

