### Randomization

Stratified permuted block randomization with a block size of 4 permutations will be used to randomize participants 1:1 to the OIC and TAU conditions. Stratification will be based on prior experience with psychotherapy (no vs positive vs negative prior experience) to ensure that individuals with heterogeneous treatment experiences are balanced in both arms. Before the first enrollment, the randomization sequences will be generated by a researcher who is not involved in the study conduction by using a web-based program. At the end of the first web-based study visit, the responsible study psychologist initially determines the type of prior experience with psychotherapy by evaluating the information given by each participant. The randomizing officer will then conduct the allocation of each pseudonymized study case according to the randomization plan. Finally, the randomizing officer will inform the respective study psychologist about the group membership on a case-by-case basis.

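### The 80% power claimed for the main effects at f=0.125 does not hold for the treatment main effect (about 35%), and 122 covers about 13% dropout, not 15%; the primary interaction test is not affected

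*Protocol article*

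**What the plan says.** The Sample Size section of the protocol article reports a G*Power calculation: "For two-tailed testing and a predetermined α level of .05", it states that "106 participants would provide 80% power to detect significant interaction and the main effects", with the effect given as "main effects of Cohen *f*=0.125 on the primary outcome". It introduces this by saying that "a small-to-medium effect size can be expected for the impact of OIC on the primary outcome". It then adds: "To compensate for an anticipated dropout rate of 15%, a total sample of 122 participants will be randomly assigned".

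The section does not give the G*Power test family, the number of measurements, the correlation among them or a nonsphericity value. The Statistical Analyses section sets out a mixed model with two arms and three time points (T0, T1, T2). The Randomization section says the trial will "randomize participants 1:1 to the OIC and TAU conditions". The last paragraph of the Introduction states the primary hypothesis as a larger rise in treatment expectations under OIC than under TAU from T0 to T2.

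**The concern.** One N, one f and one power figure are attached to three effects: the interaction, the time effect and the treatment effect. In a repeated-measures design these do not share a power. Positive correlation among repeated scores shrinks the error for within-subject effects (time and the interaction) and inflates it for the between-subject effect (treatment). An N that just suffices for the interaction will usually fall well short for the treatment main effect.

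At stake is the accuracy of a stated design property. If the trial report gives a non-significant treatment main effect beside the claim of 80% power, a reader would credit that result with more weight than it can carry. The step from 106 to 122 also looks as if it multiplied by 1.15 where it should have divided by 0.85.

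**Working it through.** **Inputs from the article.** Two-sided α 0.05, f=0.125 (f²=0.015625), N=106, 15% dropout and 122 randomized (Sample Size); two equal arms (Randomization); m=3 time points in the model (Statistical Analyses). **Assumed, not stated:** correlation ρ=0.5 and sphericity (ε=1). Power is from the noncentral F distribution.

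**1. Reproducing 106 (interaction).**
- λ = f²·N·m/(1−ρ) = 0.015625 × 106 × 3/0.5 = 9.94, with 2 and 208 degrees of freedom.
- Power is 80.7%. At N=104 it is 79.9%, so 106 is the smallest even N that reaches 80%.
- The time main effect has the same λ and degrees of freedom, hence also 80.7%.

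This setting is not the only one that fits. Two time points with ρ of about 0.59, or four with ρ of about 0.40, also give 80% for the interaction at N=106.

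**2. Treatment main effect, same N and f.**
- λ = f²·N·m/(1+(m−1)ρ) = 0.015625 × 106 × 3/2 = 2.48, with 1 and 104 degrees of freedom.
- Power is 34.5%. For 80%, N=338.

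**3. Dependence on the assumed correlation (m=3, N=106).**

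| ρ | Interaction power | Treatment power | N for 80% (treatment) |
|---|---|---|---|
| 0 | 49.5% | 59.8% | 170 |
| 0.3 | 65.5% | 41.5% | 270 |
| 0.5 | 80.7% | 34.5% | 338 |
| 0.7 | 96.0% | 29.7% | 404 |
| 0.8 | 99.6% | 27.8% | 438 |

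The alternative settings that also return 106 leave the treatment effect at 30% (two time points, ρ 0.59) or 41% (four, ρ 0.40). The highest treatment power in any setting tried was 72.2% (four time points, ρ=0), where the interaction has only 55.8%. No setting tried gives both effects 80%.

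**4. What an interaction f of 0.125 means as an arm difference.** With no baseline difference, f is half the standard deviation of the arm differences across the three time points.
- Differences (0, d, d): standard deviation 0.4714d, so d = 0.25/0.4714 = 0.53.
- Differences (0, d/2, d): standard deviation 0.4082d, so d = 0.25/0.4082 = 0.61.

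In these two cases the treatment main effect is itself larger than 0.125 (f=0.177 and 0.153), but its power at N=106 and ρ=0.5 is still only 59.8% and 48.1%.

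**5. Dropout.**
- 106 × 1.15 = 121.9, which gives the stated 122.
- Keeping 106 after a 15% loss needs 106/0.85 = 124.7, so 125, or 126 for equal arms.
- 122 × 0.85 = 103.7 remain; 1 − 106/122 = 13.1% is the loss that 122 can absorb.
- Interaction power is 79.5% at N=103 and 79.9% at N=104.

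**The case against.** The strongest reply is that the treatment main effect is not a hypothesis of this trial. The Introduction frames the primary hypothesis as a difference in change, and the treatment main effect averages in T0, before any intervention. The interaction has the claimed power, and so does the time effect, so only one of the two main effects is misdescribed. This stands, and it limits the point to the wording of a power claim.

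Three stronger readings are tempting, and the document does not support them.

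- **That the primary test is underpowered.** At f=0.125 the interaction keeps about 80% under ρ=0.5 and sphericity. With ε=0.75 it would be 72%, but nothing in the article points to that value.
- **That the small-to-medium label is wrong, because 0.53 to 0.61 SD is medium on the article's d scale.** The article uses d for pairwise comparisons and partial eta squared for explained variance, with 0.01 small and 0.06 moderate. f=0.125 converts to 0.015625/1.015625 = 0.015 directly, or to 9.94/(9.94+208) = 0.046 from the interaction λ. Both lie between small and moderate, so the label is defensible.
- **That f=0.125 means d=0.25, so that power is far lower.** The article never equates the two.

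On dropout, the shortfall is about three participants. The planned mixed model includes everyone randomized, and multiple imputation is foreseen when more than 2% of data are missing. Counting dropouts as lost entirely is therefore conservative. The arithmetic slip remains, but its effect is negligible.

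**Conclusion.** The claim of 80% power is wrong as written for the treatment main effect. The figure is about 35% with three time points and ρ=0.5, and 28% to 60% for ρ from 0.8 to 0. The exact value depends on a correlation that the article does not give; the shortfall below 80% held in every setting tried. The claim is right for the time effect and for the treatment-by-time interaction, which is the primary hypothesis, so the sample size and the primary test stand. The dropout allowance is off by a small amount: 122 covers about 13%, and a 15% loss leaves about 104 completers with just under 80% power. Overall this is a minor correction to stated figures.

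**What to change.** Keep 122. In the Sample Size section:

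1. Remove the reference to main effects, or limit the power statement to the treatment-by-time interaction, and give the number of time points and the correlation actually entered in G*Power. The three time points and 0.5 used above are an inference and should not be inserted as fact without checking.
2. State that 122 allows for about 13% dropout, or that 15% leaves about 104 completers and just under 80% power.
3. Optionally, add the implied arm difference (about 0.53 to 0.61 SD if three time points and a correlation of 0.5 were used), so that readers do not take f=0.125 for d=0.25.

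The effect-size label can stay. The cost is a few words. The stated figures become slightly less favourable, and neither the design nor the recruitment changes.

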**Figure 1 figure1:**
[figure not shown]
Anticipated study flow chart.

### Procedure

A telephone interview will take place before enrollment, in which oral study information will be given and interested persons are screened for self-reportable inclusion and exclusion criteria. If eligibility is given, interested persons will be invited for the first of the 2 web-based study visits that are conducted online by trained clinicians (Master of Science psychologists). At the first web-based study visit (T0), written information about the study will be given and the self-reportable inclusion and exclusion criteria will be queried. After providing their informed consent, participants will take part in a video-based Structured Clinical Interview for DSM-5 disorders (SCID-5) [26] to verify the indication for psychotherapy and check for exclusion criteria. If participants fulfill the eligibility criteria, the baseline assessment (T0) as well as the subsequent randomization will take place. At the end of T0, participants of both groups will receive TAU in form of an information brochure about psychotherapy. Participants will be invited to voluntarily study the brochure until the second web-based study visit (T1) 2 weeks later. At the second web-based study visit (T1), the intervention group will participate in the video-based OIC. Subsequently, all participants will take part in the postassessment and an interview for assessing the capacity to consent and adverse events. Upon request, participants will receive their individual results report of the SCID-5 within 1 week after T1. Two weeks (T2) and 3 months (T3) after T1, participants will be invited to complete 2 web-based follow-up questionnaires. A detailed summary of all the instruments is provided in Table 1.

**Table 1 table1:** Schedule of enrollment, intervention, and assessment according to Standard Protocol Items: Recommendations for Interventional Trials (SPIRIT).

						Study period								
				Screening		Enrollment		Intervention		Postallocation				
				
Time point				–1		T0				T1		T2		T3
**Screening and enrollment**														
	Study information			✓		✓								
	Eligibility screen			✓		✓								
	Informed consent					✓								
	Randomization					✓								
**Intervention**														
	Treatment as usual + optimized informed consent consultation							✓						
	Treatment as usual							✓						
**Assessments**														
	**Primary end point**													
		Treatment expectations (TEX-Q^a^)			✓				✓		✓		✓	
	**Secondary end points**													
		Capacity to consent (MacCat-T^b^ interview)							✓					
		Decisional conflict (DCS^c^)			✓				✓		✓			
		Side effects of psychotherapy: occurrence expectations, anxiety, and expected coping (3 constructed items)			✓				✓		✓			
		Autonomous treatment motivation (ACMTQ^d^ subscale)			✓				✓		✓			
		Adherence intention (3 constructed items)			✓				✓		✓			
		Interest in and knowledge about psychotherapy in general (2 constructed items)			✓				✓		✓			
		Knowledge about what is meant by psychotherapy, its effectiveness, key mechanisms, side effects, legal and organizational aspects (5 constructed items)			✓				✓		✓			
		Information-seeking behavior toward finding a treatment (3 constructed items)									✓		✓	
		Utilization of treatment services (6 constructed items)									✓		✓	
		Satisfaction with received information (CSQ-8^e^)							✓					
		(Expected) adverse events (interview)							✓		✓^f^		✓^f^	
		(Expected) serious adverse events (interview)							✓		✓^f^		✓^f^	
